### 2.5 Primary and secondary outcomes

Primary and secondary outcomes are detailed in
Table 3 for both CARE-clinical and CARE-qualitative, and also described in section 2.6.3.

**Table 3. T3:** CARE study objectives.

CARE-CLINICAL			
	Objectives	Endpoints	Assessments
Primary objectives	To assess method satisfaction in Annovera users vs. OC/DMPA at 12 and 52 weeks of use.	Proportion of participants reporting they are “highly satisfied” or “satisfied” with their method.	Acceptability questionnaires administered during follow up appointments (includes question on satisfaction with method.)
	To compare method continuation between Annovera users and OC/DMPA users at 4, 12, 24, 36, and 52 weeks.	Kaplan-Meier survival curves for method continuation over time.	Self-report of continued method use, date of and reason for discontinuation.
	To assess Annovera uptake by the proportion of women at the site during the study period who initiated Annovera vs. OC/DMPA.	Proportion of women who initiate Annovera (or OCs/DMPA) among all women who newly initiated a method at the study site during the study period.	Review of clinic records documenting all women seeking contraception during study and method selected.
Secondary objectives	To assess various dimensions of acceptability of Annovera at 4, 12, 24, 36 and 52 weeks.	Aspects to be explored include: ease of use, experience and sensation, impacts on sexual activity, as well as use patterns, likes/dislikes, hypothetical cost considerations, comparison with other methods, and plans for future method use.	Acceptability questionnaires administered during follow-up appointments, and information from assays (to compare assay-derived use vs. self-reported use).
	To determine characteristics associated with willingness to try Annovera (vs. to use other contraceptive methods).	Profiles of women who try Annovera or another method.	Baseline questionnaires (Annovera users and OC/DMPA users).
	To determine characteristics associated with satisfaction with Annovera (vs. with dissatisfaction with Annovera).	Profiles of women who are satisfied with Annovera.	Follow-up questionnaires for Annovera users.
	To assess reasons for contraceptive method selection and discontinuation in Annovera users and users of other contraceptive methods.	Comparison of reasons for contraceptive method selection and discontinuation in Annovera users and non-users.	Baseline questionnaire and discontinuation survey.

CARE-QUALITATIVE	
Primary objectives	Assessments
To assess factors influencing acceptability and perceptions of women aged 18-45 years in Kenya and Zimbabwe regarding Annovera	IDIs with women in CARE-clinical
To assess the perceptions of husbands/partners of women using Annovera about the method	IDIs with male partners of women using Annovera in CARE-clinical
To assess the perceptions and provision practices of healthcare providers regarding Annovera	IDIs with health care workers who have provided Annovera
To assess factors influencing method choice among women who do not choose Annovera and instead choose OCs or DMPA	IDIs with women using OCs/DMPA in CARE-clinical

### 2.6 Data collection, management, and analysis

*2.6.1 Data collection*

In CARE-clinical, we will collect data via source documents, Case Report Forms (CRFs), quantitative surveys, and ring assays. We developed CRFs to capture information about enrollment-related data, medical and menstrual history, concomitant medications, pelvic and physical exams, pregnancy testing and notifications, ring dispensing and return, adverse events, social harms, missed appointments, protocol deviations, and study termination. Quantitative surveys will be administered by a study staff member, either in-person or telephonically, at each study appointment. To develop these questionnaires, we drew on Sekhon
*et al.*’s contraceptive acceptability model
^
27
^ and Griffin
*et al.*’s subsequent operationalization of that model,
^
22
^ and also used or adapted some questions from prior vaginal ring
^
28–
31
^ and other contraceptive acceptability studies.
^
32,
33
^ Our questionnaires (baseline, follow-up, and early discontinuation) are available in
Appendix 3a-3c. We will also gather information from the rings that are returned to the United States after use for laboratory analysis. No human biological material will be used or stored.

For CARE-qualitative, we will conduct cross-sectional IDIs, captured using audio recorders. Study guides for CARE-qualitative were informed by similar studies on acceptability of contraceptive vaginal rings,
^
34–
36
^ and are available in
Appendix 4a-d.

For both CARE-clinical and CARE-qualitative, interviews will be conducted in English or in the national language (Kiswahili in Kenya and Shona in Zimbabwe), according to the participant’s preference.

*2.6.2 Data management*

For CARE-clinical, study data will be collected and managed using Research Electronic Data Capture (REDCap), an electronic data collection tool on a validated server hosted at the Population Council.
^
37,
38
^ REDCap is a secure, web-based software platform designed to support data capture for research studies. Queries will be triggered during data entry or by study data managers during routine data reviews. Study sites will maintain source data and documents in secure locations with limited access for the entire period of study implementation and until after the retention periods prescribed by local regulatory requirements.

For CARE-qualitative, audio-recorded interviews will be transcribed and typed in Word by the interviewers. Interviews conducted in the national language (Kiswahili in Kenya and Shona in Zimbabwe) will be transcribed directly from the national language to English by interviewers. Transcripts will be submitted to the study investigators via a secure link accessible only to members of the research team. Audio recordings will be erased once the study reports are finalized.

In line with funding requirements, data underlying any CARE publications will be anonymized and made publicly available through online data repositories. If anonymity cannot be ensured through protective measures like de-identification, or if sharing could put participants at risk of re-identification, we will seek an exception from the funding agency.

*2.6.3 Data analysis*

For CARE-clinical, we will assess three primary objectives. First, we will calculate the proportion and 95% confidence interval for
**Annovera uptake** as compared with uptake of OCs and DMPA (calculated as the number of women who initiated these methods among all women who newly initiated contraception or switched from another method at the study site during the study timeframe). We will measure the cumulative probabilities of
**continuation** of Annovera as compared with continuation of OCs/DMPA over 52 weeks, based on Kaplan-Meier methods: plotting survival curves and calculating 95% confidence intervals around the cumulative probabilities of continuation. We will calculate
**satisfaction** as the proportion of women who report being “satisfied” or “very satisfied” with Annovera versus with OCs/DMPA, based on the questionnaire administered at weeks 12 and 52. We will compare satisfaction by method and timepoint using mixed-effects logistic regression with subject and timepoint (week 12 or 52) as random effects and satisfaction as the dependent variable.

We will also assess four secondary objectives. First, we will assess the
**acceptability** of Annovera using the IVR acceptability scale (IVR-AS) which assesses ease of use, experience with the ring/sensation and effects on sex and intimacy. Other aspects from the acceptability questionnaire will also be summarized including likes/dislikes, hypothetical cost considerations, comparison with other methods, adherence, and plans for future method use. Acceptability endpoints will be summarized by time point to assess patterns over time and to determine potential subsequent analyses. We will also summarize and compare baseline characteristics among participants
**willing to try** Annovera versus those willing to try OCs/DMPA using chi-square or t-tests. Similarly, we will compare baseline characteristics among participants in the Annovera arm who reported that they were
**satisfied** or very satisfied (vs. dissatisfied or very dissatisfied) with the ring. Depending on patterns of satisfaction responses over time, we will either do this comparison using mixed-effects models to account for repeated responses, or will categorize participants by their pattern of responses (e.g. always satisfied, initially dissatisfied-then satisfied, etc.) We will compare reasons for
**contraceptive method selection** and reasons for
**discontinuation** between participants in the Annovera and OC/DMPA arms using chi-square tests.

We will assess all returned vaginal rings to evaluate the extent of discoloration, according to established visual assessment methods.
^
39
^ We will also assay approximately 50-60 returned rings for residual drug levels (segesterone acetate and ethinyl estradiol) from participants who discontinued at various timepoints. Specifically, we will aim to assay rings from approximately 6 participants (3 per site) discontinuing by each of weeks 4, 12, 24, and 36 and from approximately 30 participants (approximately 15 per site) completing the study (a total of 50-60 assayed rings out of the expected 200 used in the study). We will aim for the number of rings assayed at each time point to be similar across both study sites. We will compare residual drug (NES, EE) content of these rings against self-reported days of ring use.

All enrolled participants will be included in all analyses where they contributed data. Select analyses will also be done for the following subgroups: country (Kenya, Zimbabwe), age group (18-24, 25-35, 36-49). Missing data will be treated as missing and not imputed. A statistical analysis plan, to be completed and approved prior to data lock, will provide further detail on analysis specifications.

For CARE-qualitative, we will employ a thematic content analysis approach. This will entail coding the data, developing a list of emerging themes, categorizing themes within a hierarchical framework of main and sub-themes, looking for patterns and associations between themes, and comparing within and between participant groups. CARE-qualitative study investigators will work with two coders (per country) to develop a codebook based on the initial interviews. The coders will then use the codebook to code the remaining transcripts. Any disagreements in coding of transcripts between the two coders will be resolved through discussions between the study investigators and the coders. Insights generated from the qualitative data will elucidate some of the patterns observed in the clinical data, for example, on factors that could explain those patterns.

### 2.7 Sample size calculations

As CARE-clinical is an acceptability study, we did not develop formal statistical hypotheses nor base sample size on statistical considerations. With 200 women in each group, the standard error around a point estimate (e.g., satisfaction) would be at most 7%.

For CARE-qualitative we purposively determined sample sizes based on the minimum number of interviews that would yield saturation while ensuring representation from those using the method at the time of interview and those who stopped, in addition to considering resource constraints. Research suggests that saturation is achieved with the first 12 interviews while basic elements of meta-themes are present in the first six interviews.
^
40
^ From the Annovera arm of CARE-clinical, we will recruit up to 30 women in Kenya and 18 in Zimbabwe), and up to 6 male partners of these women in each study site. From the OC/DMPA arm of CARE-clinical, we will recruit up to 6 women in each study site. A total of 6 health care staff (about 3 in each country) providing Annovera in clinics participating in the research will be targeted for inclusion in the study; this was determined based on the number of staff offering contraceptive services in participating clinics as part of this study.

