### 2.2 Study settings and populations

CARE-clinical will recruit potential participants from non-pregnant women seeking contraception from standard service provision sites in Kibera (Nairobi), Kenya and Mbare (Harare), Zimbabwe. The Zimbabwe site is an adolescent sexual and reproductive health project run by Médecins Sans Frontières (MSF) which focuses on adolescents and young people aged 10-24. The Kenya site is a government facility that serves all ages. Participants will be aged 18-24 in the Zimbabwe site and 18-45 in the Kenya site. Across both sites, we aim to recruit approximately 200 Annovera users and 200 OC/DMPA users.

CARE-qualitative will recruit participants from the Annovera arm of CARE-clinical (up to 30 women in the Kenya site and 18 in the Zimbabwe site) for serial cross-sectional IDIs with women who are using or who have discontinued using Annovera. CARE-qualitative will also recruit potential participants from the OC/DMPA arm of CARE-clinical (up to 6 in each study site) for a one-time IDI focused on reasons for method selection. We will also recruit male partners of Annovera-using women (up to 6 male partners in each study site) and health care staff from the participating clinics providing Annovera (up to 3 staff members per site).

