Appointments 2-5 will be conducted remotely via telephone contacts to emulate the experience of not being required to return to the clinic during one year of Annovera use. If a participant does not own their own phone, a study staff member will visit the participant at a location of their choice and provide them with a phone to use for the duration of the appointment. Calls will occur at the following time points in relation to the date of enrollment: Appointment 2 = 4 weeks ± 1 week; Appointment 3 = 12 weeks ± 2 weeks; Appointment 4 = 24 weeks ± 2 weeks; Appointment 5 = 36 weeks ± 2 weeks. These calls will include procedures detailed in
Table 2, including administration of a survey anticipated to take approximately 20-30 minutes. At the end of each appointment, participants will receive the equivalent of approximately $5 USD to compensate them for their time, which may be delivered via a mobile phone-based money transfer if the participant wishes.

Appointment 6 will occur in-person at the study site between weeks 50-52 after enrollment. This visit will include procedures detailed in
Table 2, including administration of a survey anticipated to take approximately 1 hour. At this visit, women in the Annovera arm will be asked to return their ring to the clinic. Study staff will discuss options for subsequent contraceptive care during this visit with all participants. At the end of this visit, participants will receive the equivalent of approximately $10 USD per appointment to compensate them for their time.

We anticipate that a proportion of CARE-clinical participants will discontinue before a full year of use and respect the right of participants to discontinue using their contraceptive method and to discontinue study participation. Participants who stop using their contraceptive method prior to 52 weeks of use for any reason, including pregnancy, or who wish to end their participation in the study, will be discontinued from the study. They will be asked to complete the procedures outlined for the End of Study appointment (
Table 2), which will include completing an early termination survey. At the end of this visit, these individuals will receive the equivalent of approximately $10 USD to compensate them for their time. Annovera users who discontinue Annovera use due to an adverse event (AE) will continue to be followed until resolution or stabilization of the AE is documented.

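### Section 2.7 labels a 95% confidence interval half-width of about 7 points as a standard error; with 200 women per group the largest standard error of a proportion is 3.5 points

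*Protocol article*

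**What the plan says.** Section 2.2 of the protocol article sets the target: "we aim to recruit approximately 200 Annovera users and 200 OC/DMPA users". Section 2.7 then says of the sample size that "we did not develop formal statistical hypotheses nor base sample size on statistical considerations", and gives a single statement of precision: "With 200 women in each group, the standard error around a point estimate (e.g., satisfaction) would be at most 7" per cent. It mentions no confidence interval, and no other section restates or corrects the figure.

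The example named in that sentence, satisfaction, is a primary outcome. Table 3 (Section 2.5) defines it as "Proportion of participants reporting they are “highly satisfied” or “satisfied” with their method", and Section 2.6.3 says it is "based on the questionnaire administered at weeks 12 and 52".

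Two further statements bear on how many women stand behind an estimate. Section 2.4.5 says "We anticipate that a proportion of CARE-clinical participants will discontinue before a full year of use", and Section 2.6.3 says "Missing data will be treated as missing and not imputed". Section 2.4.1 plans 100 women per arm at each site, and Section 2.6.3 lists country among the subgroups for select analyses.

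**The concern.** For a binary outcome the standard error has a known ceiling that depends only on the number of women. With 200 women that ceiling is well below 7%, so the figure and its label cannot both be right.

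The study has no formal hypothesis and no power calculation, so this sentence is all a reader has for judging how informative 200 women per arm will be. Taken literally, a standard error of 7% implies 95% intervals of about 1.96 × 7 = 13.7 points either side, twice as wide as the design gives at full numbers. The literal reading therefore makes the study look less precise than it is.

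**Working it through.** **Inputs**
- n = 200 per group (Sections 2.2 and 2.7).
- The quantity is a single proportion in one arm (Table 3, satisfaction).
- Worst case p = 0.5. This is implied by the protocol giving a maximum; it is not stated.
- Confidence level 95%. Section 2.6.3 states it for uptake ("we will calculate the proportion and 95% confidence interval for" that outcome) and for continuation. For satisfaction it is assumed here.

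**Trying to reproduce 7% as a standard error**, using SE = sqrt(p(1−p)/n) at p = 0.5:

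| Quantity | n | SE |
|---|---|---|
| One arm | 200 | 3.54% |
| Both arms pooled | 400 | 2.50% |
| One arm, one country | 100 | 5.00% |
| Difference between arms | 200 vs 200 | 5.00% |
| Difference between arms, one country | 100 vs 100 | 7.07% |

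Nothing with 200 per group gives 7%. The within-country difference comes close, but the sentence specifies 200 women in each group and a point estimate, so it does not describe that quantity. Working backwards, an SE of 7% needs n = 0.25/0.07² = 51 women. With 200 women it would need a variance inflation of (7/3.54)², about 3.9. The document gives no basis for either.

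**Trying 7% as a 95% half-width at n = 200, p = 0.5:**
- Wald: 1.96 × 3.54 = 6.93 points
- Wilson: 6.86 points
- Clopper-Pearson: 7.13 points
- Two standard errors: 7.07 points

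All round to 7. The figure is a half-width.

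**How far the half-width holds as numbers fall**
- To stay at or below 7.0 points: n ≥ 0.25 × (1.96/0.07)² = 196, a loss of 2%.
- To round to 7 points: n ≥ 0.25 × (1.96/0.075)² = 170.7, so 171, a loss of about 14%.
- The protocol gives no attrition rate. As assumptions, at p = 0.5:

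| Assumed loss | n | 95% half-width |
|---|---|---|
| 10% | 180 | 7.3 |
| 20% | 160 | 7.7 |
| 30% | 140 | 8.3 |
| 40% | 120 | 8.9 |
| 50% | 100 | 9.8 |

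- If satisfaction were 80% (also an assumption), the half-width would be 6.6 points at 30% loss and 7.2 at 40%.

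**Related quantities**
- One arm in one country, n = 100, no loss: 1.96 × 5.00 = 9.8 points.
- Difference between two arms of 200: 1.96 × sqrt(0.25/200 + 0.25/200) = 1.96 × 5.00 = 9.8 points.

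**The case against.** The defence has four parts.

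1. **As a bare inequality the sentence is true:** 3.5% is at most 7%. That does not rescue it. The sentence offers 7% as the ceiling, the ceiling is half that, and the match to 6.93 shows a mislabel and not a loose bound.

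2. **The figure did not produce the sample size.** This stands. Section 2.7 says so in terms, so a reader should not infer that the target of 400 rests on a wrong calculation. Correcting the label changes no enrolment target, endpoint or analysis.

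3. **The sentence is conditional on 200 women and makes no claim about week 52.** This also stands. A reader might infer that the 7-point half-width collapses with any attrition, or that the protocol promises it at one year. Neither is supported. The worst-case bound survives down to 196 women and rounds to 7 down to 171, and it is kinder still if satisfaction is far from 50%. Nor do the documents show that the number with data at week 52 equals the number still using their method. Women who stop early are asked to complete an early termination survey (Section 2.4.5), and whether it yields usable satisfaction data depends on an appendix and an analysis plan that are not shown.

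4. **Precision for a difference or by country is not required here.** The sentence concerns one point estimate, country results are select subgroup analyses, and Section 2.6.3 leaves further detail to the statistical analysis plan. A reader might call the absence an error; it is not one.

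**Conclusion.** The term in Section 2.7 is wrong. With 200 women per group the maximum standard error of a proportion is 3.5 percentage points, and the stated 7% is the worst-case 95% half-width (6.9 points) when essentially all 200 contribute data. The label is out by a factor of about two. This rests only on n = 200, p = 0.5 as the worst case, simple binomial variance and a 95% level.

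It is a correction of wording with no consequence for the design. It is still worth making, because it is the section's only precision figure. The general caution that intervals widen when fewer women contribute data is sound and belongs in the sentence, but no particular week-52 figure can be given, because the protocol states no retention rate.

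**What to change.** Replace the sentence in Section 2.7 with:

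*With 200 women contributing data in each group, the standard error of a proportion (e.g., satisfaction) would be at most 3.5 percentage points, and the 95% confidence interval half-width at most about 7 percentage points; the half-width will be wider where fewer women contribute data (for example at most 9.8 points with 100 women, as for one arm within one country).*

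Optionally add that the 95% half-width for a difference between two groups of 200 is at most 9.8 points, since the satisfaction objective compares the arms.

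The cost is one restated sentence. Enrolment, endpoints and analyses are unchanged.

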### 2.8 Ethics and dissemination

*2.8.1 Ethics*

For CARE-clinical, the protocol (V.6.0, 10 May 2024), informed consent forms, data collection instruments, counseling materials, and recruitment materials were approved by the Institutional Review Board of the Population Council (New York, New York, USA) on 04 August 2024 number 984. In Kenya, the protocol, informed consent forms, data collection instruments (in English and Swahili), counseling materials, and recruitment materials were approved by the Scientific and Ethics Review Unit (SERU) on 09 July 2024 number 4810 at the Kenya Medical Research Institute (KEMRI). In Zimbabwe the protocol, informed consent forms, data collection instruments (in English and Shona), counseling materials, and recruitment materials were approved by the Medical Research Council of Zimbabwe (MRCZ) on 15 July 2024 number MRCZ/A/3002. We are in the process of receiving approval for the Protocol from the Mèdicines Sans Frontières Ethics Review Board (MSF ERB).

The study will be conducted in accordance with the US Code of Federal Regulations, the International Conference for Harmonisation of Technical Requirements for Pharmaceuticals for Human Use Guideline for Good Clinical Practice E6 (R2), Guidelines for Good Clinical Trial Practice in Zimbabwe (dated 30 August 2024) and local standard operating procedures at each site. The study is registered on the Pan African Clinical Trials Registry (202312652733486). The WHO trial registration data set is available in
Table 4.

**Table 4. T4:** Trial registration data for CARE-clinical.

Data category	Information
Primary registry and trial identifying number	PACTR 202312652733486
Date of registration in primary registry	December 14, 2023
Secondary identifying numbers	N/A
Source(s) of monetary or material support	Bill and Melinda Gates Foundation
Primary sponsor	Population Council
Secondary sponsor(s)	N/A
Contact for public queries	[name]
Contact for scientific queries	[name]
Public title	Contraceptive Acceptability REsearch (CARE)
Scientific title	Assessing acceptability of Annovera contraceptive vaginal ring use (compared to other contraceptive method use) among women seeking family planning services
Countries of recruitment	Kenya, Zimbabwe
Health condition(s) or problem(s) studied	Contraceptive acceptability
Intervention(s)	Annovera vaginal ring versus oral contraceptive pills or contraceptive injections
Key inclusion and exclusion criteria	See registration
Study type	Comparative non-randomized acceptability study
Date of first enrollment	16 October 2024
Target sample size	400
Recruitment status	Recruiting
Primary outcome(s)	Method uptake, method continuation, and method satisfaction
Key secondary outcomes	Various domains of acceptability, characteristics associated with willingness to try Annovera, characteristics associated with satisfaction with Annovera, reasons for contraceptive method selection and discontinuation.

For CARE-qualitative, the protocol and amendments (dated June 22, 2023), informed consent forms, and study guides were approved by the Institutional Review Board of the Population Council (New York, New York, USA) on 25 October 2023 number 1026. In Kenya, the protocol and amendments (Protocol ESRC P1543/2023) was approved by AMREF Ethics and Scientific Review Committee on 30 November 2023. In Zimbabwe, the protocol was approved by the MSF ERB on 29 February 2024 number 2372, and at the time of submission of this paper, additional approvals are ongoing.

*2.8.2 Conflict of interests*

Annovera was developed by the Population Council and is currently licensed by Mayne Pharma for the US market.

*2.8.3 Access to data*

A data sharing agreement between the Population Council, MSF, KEMRI, and the Harare Health Research Consortium (HHRC) will be signed for CARE data, stating that the parties may share study datasets and confidential information with each other pursuant to the terms of the agreement, and solely for the purposes of carrying out the study objectives. Any other use or transfer to any third party will require prior and written approval of all other parties, and as required by applicable laws and the competent authorities in each country. As described above, and in line with funding requirements, data underlying any CARE publications will be anonymized and made publicly available through online data repositories, subject to any applicable ethical, legal, or regulatory requirements or restrictions.

*2.8.4 Post-trial care*

Annovera users in CARE-clinical who wish to continue using Annovera after the study ends will be offered Annovera free of charge for a period of three years post-study. Prior to the end of the study, we will develop a plan to ensure this three-year post-study access via an appropriate participant program (e.g., an expanded protocol), based on feasibility assessment and feedback from research centers. We will also ensure compliance with country-specific regulations and laws.

If a CARE-clinical participant needs treatment because of an injury sustained through study participation, important health services and short-term medical assistance and treatment will be available for free immediately as deemed by the study doctors. We will not offer monetary compensation for any services, but healthcare discussion and appropriate referrals to other healthcare services will be available.

*2.8.5 Dissemination*

The CARE study team will periodically update the study communities and Community Advisory Boards about progress during study implementation. On completion, results will be presented locally to study participants, community advisory boards, and other local stakeholders, as well as shared at national and international meetings and conferences. Manuscripts will be submitted to peer-reviewed journals and made available via Open Access terms, as per funder policy. An authorship committee including representatives from each entity participating in study implementation will be responsible for collaboratively ensuring equitable collaboration and ethical authorship practices, including adherence to International Committee of Medical Journal Editors (ICMJE) guidelines.

